#### Patient timeline (Fig. 2)

**Fig. 2 Fig2:**
[figure not shown]
Schedule of evaluations. *To be monitored continuously throughout study until study is closed to enrollment. Abbreviations: *BP* blood pressure, *BM*I Body Mass Index (weight(kg)/height(m)^2^), *CEQ* Credibility/Expectancy Questionnaire, *HR* heart rate, *DSSI* Duke Social Support Index, *IRLS* International Restless Legs Scale, *PASE* Physical Activity Scale for the Elderly, *POMS* Profile of Mood States, *PSQI* Pittsburgh Sleep Quality Index, *PSS* Perceived Stress Scale, *SF-36* 36-item MOS Short Form-36, *Tx* treatment

### Data management

Completed data forms or other hard-copy documents containing protected health information will be kept in a locked file in an investigator’s office. Data will be entered into an electronic deidentified database by authorized study team members, checked for completeness and accuracy. The PI or study staff will review all data collection forms on an ongoing basis for data completeness and accuracy as well as protocol compliance. Access to data with identifiers will be restricted to authorized study team members and regulatory authorities. Data verification will be performed by someone other than the individual originally collecting the data, or by double-data entry.

Electronic data will be stored on a secure server which is maintained, with regular back-ups, by WVU Health Sciences Center system administrators and accessible from password-protected computers in the WVU Department of Epidemiology. Any data, forms, and other records with identifiers that leave the site will be transported in a locked file box to maintain confidentiality. Identifiable data will be destroyed 5 years after study completion or 3 years after the last publication based on when the data is published, whichever comes last (unless future regulations dictate that the data be kept for longer).

### Statistical methods

All analyses will be performed using SAS [145] or R [146]. For the primary feasibility aims, we will be evaluating recruitment and enrollment rates (all interested potential participants), acceptability of randomization (all enrolled subjects), retention, and adherence (all randomized participants). For the secondary aims, we will define the intent-to-treat (ITT) population as all subjects who are randomized with baseline assessments and at least one post-randomization assessment. The per-protocol analysis of the exploratory outcomes (RLS symptoms, sleep quality, mood, stress, and quality of life) will include all participants who completed both assessments and at least 75% of the classes.

*Feasibility of the proposed design* (*A.1*) will be evaluated in several ways:

*Recruitment*: we will examine recruitment time and success rates for different recruitment strategies and assess the percentage of interested volunteers who meet the study criteria, agree to participate and are randomized. We will use Fisher’s exact test to determine whether there are any differences in recruitment rates across the different strategies, and exponential regression model to assess the recruitment strategy on recruitment time.

*Retention*: will initially be assessed using descriptive statistics, including comparisons between retained individuals and drop-outs. The nonparametric Kaplan-Meier curve will be used to estimate the probability of retention over the duration of the study. If retention is unexpectedly low, we will use the proportional hazard model to assess retention differentials by treatment, demographic, and health-related factors to better target and retain specific groups in future trials.

*Randomization success*: (i.e., the two groups are similar demographically and on anthropometric and exploratory outcome measures at baseline) will be assessed using the one-sample run test. To evaluate *adherence* to the study protocol, we will determine missing-data rates at baseline and follow-up, class attendance (both groups), and completion of weekly logs.

*Treatment fidelity* (*A.2.1*) will be monitored and lapses recorded and compared between groups, along with outcomes of remediation strategies. We will use the Fisher’s exact (continuous data) and chi-square tests (using benchmark cut-offs) to determine potential differences in treatment adherence and fidelity.

*Treatment effect sizes* (*A.2.2*), based on between-group differences in change over time, will be estimated using one-way ANOVA models. Effect size estimates will be calculated using both ITT (primary) and per-protocol analyses. These unbiased estimates of intervention effect size will inform sample size determination for our planned future efficacy trial [147]. Scores on *the Yoga-dosing Questionnaire* (*A.2.3*) will also be assessed using descriptive statistics to determine optimal scheduling and maximum acceptable dosing of yoga for our future trial.

*Missing data*: every effort will be made to minimize missing data relevant to all aims. If missing data does occur and the missing-data pattern (probability model) is not missing completely at random (MCAR), then we will consider approaches appropriate for missing at random (MAR) and missing not at random (MNAR). If the pattern or structure of the plausible missing data suggests MAR, either the EM algorithm [148], inverse weighting [149], or multiple imputation (MI) [150, 151] will be used and the missing-data mechanism will be constructed from the collected data [150, 152, 153]. The selected method will reflect the appropriateness of the method to best estimate the underlying missing-data mechanism [148–150, 152]. Participant characteristics will be assessed, including demographic and lifestyle characteristics, RLS severity, medical history, health-related factors, and baseline questionnaire scores for the estimation of plausible models (i.e., MCAR, MAR, and MNAR) for the missing-data mechanism. While we will not be able to definitively test if the missing data are MNAR, If there are indicators suggestive of MNAR (e.g., drop-outs differ significantly from non-drop-outs in key characteristics), we will use MI in conjunction with a sensitivity analysis to provide a set of plausible conclusions recognizing that each conclusion will be predicated on the assumptions necessary for constructing a MNAR missing-data mechanism model [150, 153].

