#### Secondary objectives

Our secondary objectives include the assessment of treatment fidelity in the two programs, as well as participant willingness to enroll in yoga programs of varying duration and intensity. In addition, we will measure RLS symptom severity, sleep quality, mood, and health-related quality of life at baseline and 12 weeks to obtain effect size estimates for these exploratory outcomes. This information will provide critical data on which to base our planned larger RCT to determine the efficacy of yoga as a potential therapy for RLS. Secondary aims are as follows:Aim.2.1. Monitor and assess treatment fidelity in the yoga and educational film programs, using specific metrics to gauge fidelity. Lapses in fidelity will be recorded and the data used to inform strategies to address these lapsesAim.2.2. Assess the effect sizes at week 12 of a beginner yoga and a structured educational film program for RLS symptoms and related key exploratory outcomes (sleep quality, mood, perceived stress, and health-related quality of life) in adults with moderate to severe RLS, using well-validated, self-report instruments commonly employed in evaluating RLS treatments. Effect size estimates for these exploratory outcomes will provide critical data on which to base sample sizes in future larger trials, as well as provide important preliminary information on sensitivity of specific endpoints to change with a 12-week yoga interventionAim.2.3. Determine acceptable doses of yoga for a trial by assessing participant willingness to complete, as well as preference for yoga programs of the following duration and intensity: 8 weeks, 16 classes (2x/week); 12 weeks, 16 classes (2x/week for first 4 weeks, 1x/week thereafter); 16 weeks, 16 classes (1x/week). Acceptability and preferences will be evaluated using a self-report questionnaire administered to all participants at the follow-up assessment visit

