Data on exploratory outcomes and certain modifying/confounding factors will be collected at baseline and 12 weeks to determine the effect sizes of the programs, data critical to the design of the planned larger RCT. RLS symptom severity, the primary efficacy outcome for the full-scale trial, will be evaluated using the International RLS Rating Scale (IRLS), a 10-item scale which includes questions related to frequency, intensity, and impact [89]. Considered the gold standard for measuring RLS symptoms [109, 110], this instrument is recommended for use in RLS clinical trials by the European RLS Study Group (EURLSSG) [111], and is widely used both in the US and internationally [3, 112]. Additional exploratory outcomes are sleep quality, mood, and health-related quality of life (HrQOL), endpoints recommended for inclusion in all clinical trials of RLS [26, 111]. These outcomes will be assessed via a short battery of self-report instruments commonly used in pharmaceutical trials of RLS patients [113–116]. Sleep quality will be assessed using the nine-item Pittsburgh Sleep Quality Index (PSQI) [117]; mood will be evaluated using the 65-item Profile of Mood States (POMS) [118] and 10-item Perceived Stress Scale (PSS) [119, 120]; and HrQOL will be measured using the 36-item MOS Short Form-36 (SF-36) [121, 122]. These self-report instruments are well-established scales that have been shown to be sensitive to short-term behavioral interventions, and have been validated in a wide range of populations, including RLS patients [118, 123–137]. As in our previous trials [15, 66] we will also assess potential changes in blood pressure and heart rate to determine effect sizes in these indices of sympathetic activation; heart rate and blood pressure will be measured three times at each assessment using an automated blood pressure monitor (Omron HEM-780) after a 5-min seated rest period.

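### The ITT set for the effect-size aim admits only participants assessed at week 12, which conflicts with the protocol's missing-data plan and its claim of unbiased estimates

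*Protocol article*

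**What the plan says.** Under Statistical methods, the protocol article sets one population for each group of aims. Retention and adherence use everyone randomized. The secondary aims use an "intent-to-treat (ITT) population as all subjects who are randomized with baseline assessments and at least one post-randomization assessment". The per-protocol set for the exploratory outcomes is "all participants who completed both assessments and at least 75% of the classes".

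On timing, Data collection and outcomes states: "Data on exploratory outcomes and certain modifying/confounding factors will be collected at baseline and 12 weeks". Secondary objectives agrees: the measures are taken "at baseline and 12 weeks to obtain effect size estimates for these exploratory outcomes".

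Still under Statistical methods, effect sizes come from one-way ANOVA on between-group differences in change. The ITT set is primary for these estimates and the per-protocol set is also reported. The protocol adds: "These unbiased estimates of intervention effect size will inform sample size determination" for the later efficacy trial. The missing-data paragraph continues: "If the pattern or structure of the plausible missing data suggests MAR, either the EM algorithm", with inverse weighting and multiple imputation (MI) as the alternatives. It also plans MI with a sensitivity analysis for data missing not at random (MNAR), to be used if, for example, drop-outs differ significantly from the others in key characteristics.

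**The concern.** A set that requires a post-randomization measurement is selected on something that happens after randomization. Where there is only one follow-up, that requirement amounts to having the outcome observed, and the ITT label no longer describes the set. The protocol also plans methods meant to bring drop-outs into the analysis, so two analysts could follow the same section and report on different people: those with a week-12 visit, or all 44.

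What is at stake is the effect size that will be used to plan the efficacy trial. Participants know their arm, the main outcomes are self-reported, and the programs differ in burden: 16 classes plus home practice against 12 classes plus a daily log. Staying to week 12 could therefore depend on arm and on response. If it does, the difference among attenders is not the difference among all randomized, and the next trial could be sized on too large an effect.

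**Working it through.** **Step 1. Which condition restricts the set?** Baseline data are collected before randomization (Data collection and outcomes; Randomization), so every randomized participant should have them. The condition that removes people is the post-randomization assessment.

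**Step 2. How many such assessments are there?** Exploratory outcomes are taken at baseline and week 12. The per-protocol definition speaks of both assessments, which means two. Data collection and outcomes defines retention as completing the assessment visits. The only post-randomization outcome assessment described is week 12, so a participant without that visit is outside the ITT set.

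**Step 3. The plan's own figure.** Sample size gives 44 with 20% attrition. The simulation cannot be rerun, because its effect sizes, standard deviations and precision target are not given. The attrition step can be checked: 35 / (1 − 0.20) = 43.75, rounded up to 44. This fits a post-attrition sample of about 35, and the section says the ITT ANOVA was sized on the post-attrition number.

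**Step 4. How many are omitted?** Analysed = 44 × (1 − attrition).

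| Attrition (Sample size) | Analysed | Omitted |
|---|---|---|
| 20% | 44 × 0.80 = 35.2 | 44 × 0.20 = 8.8, about 9 |
| 30% | 44 × 0.70 = 30.8 | 44 × 0.30 = 13.2, about 13 |

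**Step 5. What is left for each missing-data method on A.2.2?**

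- EM and MI for an absent week-12 visit: nothing, because everyone in the set has the visit.
- EM and MI for missing items or scales among attenders: still usable.
- Inverse weighting: usable. It analyses the observed cases and uses drop-outs only to model the probability of being observed.
- The comparison of drop-outs with the rest, which prompts the MNAR analysis: it can be tabulated, but MI on the stated set would have no drop-outs to impute.

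**Step 6. Illustration of what selection could do.** Everything in this step is assumed; the documents give only overall attrition. Let attenders improve by 0.8 SD on yoga and 0.3 SD on film, and let drop-outs not change. The attender difference is 0.8 − 0.3 = 0.50 SD. The all-randomized difference is (1 − yoga drop-out) × 0.8 − (1 − film drop-out) × 0.3.

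- 20% in each arm: 0.80 × 0.8 − 0.80 × 0.3 = 0.40 SD.
- 30% yoga, 10% film (20% overall): 0.70 × 0.8 − 0.90 × 0.3 = 0.29 SD.

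If film attenders improve by 0.2 SD instead and the attender difference stays at 0.50, the results are 0.80 × 0.7 − 0.80 × 0.2 = 0.40 and 0.70 × 0.7 − 0.90 × 0.2 = 0.31. If all drop-outs changed as attenders in their arm did, the difference would be 0.50 and there would be no bias.

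**Step 7. Scale against precision.** The approximate 95% half-width for a standardized difference d is 1.96 × √(2/n + d²/(4n)), with n per arm. At d = 0.5 it is 0.60 for n = 22, 0.66 to 0.68 for n = 18 or 17, and 0.73 for n = 15. The illustrated bias of 0.10 to 0.21 SD lies well inside that uncertainty.

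**The case against.** The strongest reply has four parts.

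**The missing-data plan can still operate.** A reader might infer that the ITT definition and the missing-data paragraph cannot both be carried out. The documents do not support that. Inverse weighting is one of the named options and can run on the observed cases, and item-level gaps among attenders remain. The paragraph also covers all aims, including logs for the feasibility aims. What stands is narrower: two of the three named methods have no missing week-12 visits to handle, and the section does not say which set the methods apply to.

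**The set is not one of program completers.** A reader might equate it with people who finished the intervention. The section on discontinuing allocated interventions says participants who stop may still be followed, with their permission. If they attend week 12 they are in the ITT set, and only the per-protocol set requires 75% of classes. The right description is available-case.

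**Another contact might count as an assessment.** The expectancy questionnaire is collected after the first class, logs are weekly, and the program evaluation can be completed on leaving. Confidentiality speaks loosely of regular intervals, and the schedule in Fig. 2 is not shown. None of these is described as an outcome assessment, and the protocol uses the word for its two visits. On the wide reading some drop-outs would enter the set, but the definition would still need clarifying.

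**The bias is assumed, and imputation may not remove it.** This stands. A reader might take the step from 0.50 to 0.40 or 0.29 SD as an estimate of the trial's bias; it is only an MNAR illustration. With one follow-up, imputation under missing at random (MAR) from baseline scores would largely reproduce the attender difference in that scenario. Attendance and log data help only as far as they predict the outcome.

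**Conclusion.** The point holds for Aim 2.2. The set named ITT, which is primary for the effect sizes, contains only participants with a week-12 assessment. It leaves out about 9 to 13 of 44 at the protocol's stated attrition. That conflicts with a missing-data plan directed at drop-outs and with describing the estimates as unbiased. The conclusion rests on reading the post-randomization assessment as the week-12 visit, the only outcome assessment the text describes after baseline.

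The direction and size of any bias are unknown. A reader might also infer that the trial's main results are compromised. They are not: retention and adherence are evaluated in everyone randomized, and ITT is primary only among the effect-size analyses, for outcomes the protocol calls exploratory. The wide intervals limit what these estimates can support in any case, although they neither reveal nor remove bias. This should be fixed, at a level below a flaw in the primary analysis.

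**What to change.** 1. Define the ITT population for the secondary aims as all randomized participants, analysed in the arm assigned, with no condition on post-randomization data.
2. State that the planned MAR method applies to missing week-12 scores, by arm, using baseline scores and attendance and log data.
3. Keep the planned MNAR sensitivity analysis and run it whenever week-12 outcomes are missing, not only when drop-outs look different. With about 9 drop-outs, a non-significant comparison is weak reassurance, and MAR imputation alone would not remove bias from outcome-dependent drop-out.
4. Report the present set as a sensitivity analysis labelled available-case.
5. Remove the word unbiased from the effect-size paragraph and state the missing-data assumptions there instead.

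The cost is a change of wording and slightly more analysis, using methods the protocol already names. The estimates will rest openly on missing-data assumptions and may be less favourable. With at most 22 per arm, the imputation model will have to stay small. No extra data collection is needed.

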#### Inclusion criteria

Study participants will be ambulatory adults ≥ 1 years of age with moderate-severe RLS, defined as:Symptoms that meet all five of the International RLS Study Group’s essential diagnostic criteria for RLS [1, 88] (i.e., (1) an urge to move the legs, often associated with discomfort or disagreeable sensations in the legs, that (2) begins or worsen during periods of rest or inactivity; (3) is partially or totally relieved by movement; (4) is worse or only occurs in the evening or night; and (5) is not solely accounted for by another condition (e.g., leg cramps, positional discomfort, habitual foot-tapping))RLS symptoms at least 1x/week for the previous 3 monthsA score of at least 2 points (moderate) IRLS question 6: “How severe was your RLS as a whole?” [89, 90]; andConfirmation of RLS diagnosis and study eligibility by a physician trained in sleep medicine; these criteria will help ensure exclusion of mimics (e.g., leg cramps, positional discomfort, arthritis pain, etc.) [20, 91]. Additional criteria include: willingness and ability to complete the 12-week yoga or educational film program and all study assessments; and willingness to avoid use of any new drugs or treatments other than the assigned intervention.

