#### Exclusion criteria

Exclusion criteria are as follows: practiced yoga within the past year; currently on anti-psychotic medication; changed dosage of dopaminergic agents (e.g., levodopa, ropinirole, pramipexole) or any other central nervous system agents (e.g., sedative hypnotics, GABA analogs, narcotic analgesics, antiadrenergic agents, or anticonvulsants) within the past 3 months; hemoglobin (Hb) < 12 g/dL for women,< 13 g/dL for men; any orthopedic, neurologic, or other condition that might prevent safe completion of a 12-week yoga program or confound assessments (e.g., neuropathy; Parkinson’s disease; stroke; rheumatoid arthritis; renal failure; sleep apnea; recent (within the last 6 months) myocardial infarction; heart failure; cancer (other than non-melanoma skin cancer); pregnancy, or within 6 months post-partum). These medical exclusion criteria are consistent with those commonly employed in trials of RLS drugs and other RLS interventions [54, 92–96].

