### Interventions

#### Yoga program (active intervention)

Participants randomized to the yoga group will complete a gentle *Iyengar* yoga program based on that developed and successfully implemented in our pilot studies [15, 66]. The yoga program was finalized following detailed review and input from an *Iyengar* Master Trainer.

Program logistics: yoga group participants will attend two 75-min classes per week for the first 4 weeks, then one 75-min class for the remaining 8 weeks, and will be asked to complete a 30-min homework routine 5 days/week on non-class days. Yoga classes will be held at two yoga studios in close proximity to the WVU Health Sciences Center campus (WVU site) and OSU Center for Integrative Health and Wellness (OSU site), respectively. As in our previous trials [15, 66], each yoga class will begin with simple yogic centering and breathing exercises, followed by a sequence of active and restorative poses, and ending with a 10-min guided supine relaxation practice. The yoga routines, including a collective total of 25 common *asanas*, have been tailored for sedentary adults naïve to yoga, gradually increasing in difficulty as students progress. Pose modifications and props (e.g., chairs, blankets, and straps) will be used as needed to enable participants to perform the poses safely and easily, regardless of their level of physical ability or fitness. In addition, each class will be restricted to no more than 12 participants to allow for personalized attention. The home practice (see Table 1) will be performed with the aid of a yoga DVD and a comprehensive, indexed training manual illustrating the homework routines; These guides are based on materials developed for our preliminary trials and modified to reflect the extension to a 12-week intervention period for the proposed study. Participants will also be provided yoga mats and straps to facilitate home practice.

**Table 1 Tab1:** Yoga home practice routines

Home Practice 1: Weeks 1–3 (*use wall for side-angle standing poses*)	
1. Upward extended-leg pose	*Urdhva Prasarita Padasana*
2. Straight-leg pose: (a) bent knee 3x, (b) straight leg 2x	*Supta Padangusthasana*
3. Upward extended arms in mountain pose: (a) palms forward, (b) palms facing	*Urdhva Hastasana in Tadasana*
4. Extended side-angle pose	*Utthita Parsvakonasana*
5. Half-intense pose: (a) hands to wall, (b) hands on chair	*Ardha Uttanasana*
6. Extended triangle pose	*Utthita Trikonasana*

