#### Relevant concomitant care and interventions that are permitted or prohibited during the trial

As noted above, exclusion criteria include the use of anti-psychotic agents and change in dopaminergic or other central nervous system agents within the previous 3 months; any change in medication use or dosage during the trial will be monitored. In addition, participants are asked to avoid the use of any new drugs or treatments other than the assigned intervention, and are not allowed to participate in another intervention study for the duration of the trial. No concomitant interventions are required.

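### The plan calls its per-protocol effect size unbiased and uses it to size the next trial, but that set is selected on attendance after randomization

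*Protocol article*

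**What the plan says.** The Statistical methods section of the protocol article defines two sets for the secondary aims. The ITT population is the randomized participants who have baseline assessments and at least one assessment after randomization. The per-protocol analysis "will include all participants who completed both assessments and at least 75% of the classes".

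Under treatment effect sizes (A.2.2), the same section says: "Effect size estimates will be calculated using both ITT (primary) and per-protocol analyses". The next sentence reads: "These unbiased estimates of intervention effect size will inform sample size determination for our planned future efficacy trial". No other estimates stand between the two sentences, so the plural in the second refers to both analyses named in the first.

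On the yoga dose, the section on the yoga program prescribes "two 75-min classes per week for the first 4 weeks, then one 75-min class for the remaining 8 weeks", plus a 30-minute home routine on five days a week. The film program is one 75-minute class a week for 12 weeks.

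**The concern.** An effect size can only be unbiased for a stated target, and the per-protocol estimate fails for both targets a reader would have in mind.

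- **The effect of being assigned to yoga rather than film.** Randomization protects this contrast only while the compared groups are those it formed. Choosing participants by attendance gives up that protection, because people who keep attending may differ in prognosis or response from those who stop. A program of physical practice and a program of films need not lose the same kind of person or the same share.
- **The effect of yoga practised as prescribed.** The set asks only for classes and assessments. Most of the prescribed yoga time is at home and plays no part in who is included.

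The stake is the next trial. A planner who reads that both estimates are unbiased has no stated reason to prefer one when they differ. If the larger is picked and attendance has inflated it, the efficacy trial will be too small.

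**Working it through.** The plan states no figure for the per-protocol set, so there is nothing to reproduce. Parts 1 to 3 use the document alone. Part 4 uses assumed inputs.

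**1. What the 75% threshold asks of each arm**
- Yoga: 2 × 4 weeks + 1 × 8 weeks = 16 classes; 0.75 × 16 = 12 classes, or 12 × 75 = 900 minutes.
- Film: 12 classes; 0.75 × 12 = 9 classes, or 9 × 75 = 675 minutes.

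**2. Share of the yoga dose that the set ignores**
- Classes: 16 × 75 = 1,200 minutes.
- Home practice: 12 weeks × 5 days × 30 minutes = 1,800 minutes.
- Total 3,000 minutes; home share 1,800 / 3,000 = 60%.
- Lowest qualifying dose, with no home practice: 900 / 3,000 = 30%.
- The abstract can be read as asking for home practice on every non-class day. That gives (4 × 5 + 8 × 6) × 30 = 2,040 home minutes and a total of 3,240. The home share is then 63% and the lowest qualifying dose 900 / 3,240 = 28%.

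**3. What separates the two analysis sets**

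The exploratory outcomes are measured at baseline and week 12 only. For these outcomes the ITT set as defined therefore already needs a week-12 assessment. The extra condition that makes the second set per-protocol is class attendance, which is known only after randomization.

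**4. Illustration that the word can fail (assumed inputs)**

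Suppose the true effect is zero, outcomes have SD 1 and attendance has correlation ρ with outcome. Suppose also that 75% of the yoga arm and 90% of the film arm meet the threshold. For a normal variable, keeping the top share k shifts the mean outcome by ρ × φ(z) / k, where z is the cut-off and φ the normal density.
- Yoga, k = 0.75: 0.3178 / 0.75 = 0.424, so the shift is 0.127 at ρ = 0.3 and 0.212 at ρ = 0.5.
- Film, k = 0.90: 0.1755 / 0.90 = 0.195, so the shift is 0.058 at ρ = 0.3 and 0.097 at ρ = 0.5.
- If attendance tracks outcome in both arms, the per-protocol estimate is about 0.07 (ρ = 0.3) to 0.11 (ρ = 0.5) SD.
- If it does so in the yoga arm only, the estimate is about 0.13 to 0.21 SD.

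ITT with complete data stays at zero. If both arms kept the same share with the same correlation, the shifts would cancel. The illustration therefore shows that lack of bias is not assured, not that a particular bias will occur.

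To see what this could do to planning, take a true effect of 0.5 SD, 80% power and two-sided 5%. Then n per arm = 2 × (1.960 + 0.842)² / d² = 15.70 / 0.25, or 63. An estimate inflated by 0.069 gives 15.70 / 0.569² = 48.5, or 49. One inflated by 0.212 gives 15.70 / 0.712² = 31.0, or 31.

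**The case against.** The strongest reply is that ITT is labelled primary, the outcomes are exploratory, and the per-protocol rule is stated openly, so nobody is misled about who is in the set. On this view the word is a slip about a supporting analysis. Most of that stands and limits the size of the point. It does not remove it: the sentence is wrong as written for one of the two analyses it covers, and the section does not say which estimate will size the next trial.

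A second reply is that the 30% dose is an extreme case and that instructors collect logs weekly and follow up non-adherence. This also stands. The figure is the floor that the rule allows, not a forecast.

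A reader might go further and infer that the set is wrongly composed and must exclude three groups. The document does not support that.

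- **Participants whose drug dose changes.** The exclusion for those who "changed dosage of dopaminergic agents" or other central nervous system drugs covers the three months before entry. During the trial, "any change in medication use or dosage during the trial will be monitored"; a change in the dose of an existing drug is not stated to be a deviation.
- **Film participants who try yoga.** It is true that "participants are asked to avoid the use of any new drugs or treatments other than the assigned intervention". But the film program teaches behavioral and complementary approaches, shows a segment on yoga as therapy, and has participants log what they try as a result. Some uptake is foreseen and arguably belongs to the comparator.
- **Yoga participants with little home practice.** The 75% home-practice figure in Aim 1b is a benchmark for the acceptability of the program, not a threshold for each participant. Applying it would select the yoga arm alone more heavily.

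**Conclusion.** The point holds for the claim, not for the make-up of the set. The plan attributes lack of bias to an estimate from participants chosen by attendance after randomization, with different class demands in each arm and no regard to 60% of the prescribed yoga minutes (63% on the alternative reading). That is an error in the text, and it matters because the estimates feed the next sample size.

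The effect is limited to a secondary estimate used for planning. The feasibility aims are untouched. No bias size is claimed: the document gives no attendance rates by arm and no link between attendance and outcome. The 0.07 to 0.21 SD above rests wholly on assumed values. Direction is open too, since missing home practice may shrink the contrast while selection on attendance may inflate it.

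Two further inferences should be resisted. Yoga use in the film arm does not bias the ITT contrast, which compares assignment to yoga with assignment to this film program, whatever film participants take up. Nor should the ITT estimate be called unbiased without qualification. As defined, it needs a week-12 assessment for these outcomes, so it relies on the planned missing-data methods for those who drop out. Sample size already assumes 20% attrition, which leaves 44 × 0.8 = 35.2 participants in all.

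**What to change.** In the treatment effect sizes paragraph (A.2.2) of Statistical methods:

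1. Do not apply the word unbiased to the per-protocol estimate.
2. State that the sample size of the efficacy trial will be based on the ITT estimate, using the section's missing-data methods for randomized participants without week-12 data.
3. Report the per-protocol result as supportive only, and describe it as an analysis of completers with at least 75% class attendance.

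This costs a few sentences and needs no new data, form or visit.

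Adding conditions on home practice, co-treatment or drug changes is a design choice for the investigators, not a correction. It would bring the set closer to the prescribed program: 75% of home practice, for example, would raise the yoga floor to 900 + 1,350 = 2,250 of 3,000 minutes, or 75%. It would also select more strongly, from about 17.6 completers per arm if the 20% attrition falls equally, and would still not make the estimate unbiased.
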